## Abstract

**Background:**

Patient-centered care is respectful of and responsive to individual patient preferences, needs, and values. To provide patient-centered care, clinicians need to know and incorporate patients’ context into their communication and care with patients. Patient contextual data (PCD) encompass social determinants of health and patients’ needs, values, goals, and preferences relevant to their care. PCD can be challenging to collect as a routine component of the time-limited primary care visit.

**Objective:**

This study aims to determine if patient-provider communication and patient activation are different for patient users and patient nonusers of an electronic health record (EHR)–integrated PCD tool and assess if the impact of using PCD on patient-provider communication and patient activation differs for Black and White patients.

**Methods:**

We describe a randomized controlled trial of a prospective cohort of non-Hispanic White and Black patients who receive primary care services at a midwestern academic health care system in the United States. We will evaluate whether providing PCD through a consumer informatics tool enhances patient-provider communication, as measured by the Communication Assessment Tool, and we will evaluate patient activation, as measured by the Patient Activation Measure for PCD tool users and nonusers. Furthermore, owing to racial disparities in care and communication, we seek to determine if the adoption and use of the tool might narrow the differences between patient groups.

**Results:**

The trial was funded in November 2017 and received local ethics review approval in February 2019. The study began recruitment in April 2019 and enrollment concluded in October 2019 with 301 participants. The analysis was completed in May 2020, and trial results are expected to be published in winter 2020.

**Conclusions:**

Recently, there has been increased attention to the role of health information technology tools to enable patients to collaborate with providers through the sharing of PCD. The adoption of such tools may overcome the barriers of current EHRs by directly engaging patients to submit their contextual data. Effectively, these tools would support the EHR in providing a more holistic understanding of the patient. Research further supports that individuals who have robust digital engagement using consumer informatics tools have higher participation in treatment follow-up and self-care across populations. Therefore, it is critical to investigate interventions that elicit and share patients’ social risks and care preferences with the health care team as a mechanism to improve individualized care and reduce the gap in health outcomes.

**Trial Registration:**

ClinicalTrials.gov NCT03766841; https://clinicaltrials.gov/ct2/show/NCT03766841

**International Registered Report Identifier (IRRID):**

RR1-10.2196/20309

## Introduction

### Background

Over the past few decades, health care has been shifting from a paternalistic to patient-centered model that values patient engagement and shared decision making [1,2]. These values align with the patient-centered care model, where clinicians provide care that is tailored to the distinct needs of the patient. It is based on the development of respectful and dignified therapeutic relationships [3].

To provide patient-centered care, clinicians need to know and incorporate the patients’ context into their communication and care with patients. Patient contextual data (PCD) encompass social determinants of health (SDH) [4] and further comprise patients’ needs, values, goals, and preferences relevant to their care [5]. In the primary care setting, clinicians address most patients’ health care needs through a sustained partnership with patients and within the context of family and community [6]. Therefore, care teams must have access to data about the patients’ perspectives, values, and other contextual considerations to tailor patient-centered conversations and clinical decisions [1,6,7]. PCD can facilitate team-based care by enabling health care team members to build a rapport quickly and to connect with patients on a humanistic level [8].

Evidence suggests that connecting with patients can bolster patient activation. In a cross-sectional study, individuals at the highest level of activation (level 4) received relevant preventative cancer screenings, had 5 of 6 clinical indicators in the normal range, and did not engage in unhealthy behaviors (tobacco smoking and obesity) at statistically significantly higher rates compared with individuals in the lowest level of activation (level 1) [9]. A longitudinal study affirmed the results that indicated that people at the highest level of activation had significantly higher odds of guideline-concordant high-density lipoproteins and serum triglyceride levels, normal Patient Health Questionnaire-9 scores, not smoking, not being obese, having no Emergency Department visits, and having no hospitalizations in the 2-year follow-up period compared with people at the lowest levels of activation [9,10]. These outcomes translated to lower health care costs, with a projected 31% decrease in costs for people who were most activated (level 4) than those who were least activated (levels 1 and 2) [10].

Despite evidence indicating that connecting with patients improves patient outcomes and reduces health care costs [9,10], PCD are often not collected as a routine component of care [11]. A barrier to the integration of PCD is linked to the current limitation of electronic health record (EHR) systems in integrating and facilitating the retrieval of social risks and care preference data [12], even if collected as unstructured data within clinical notes. Clinicians face several limitations in terms of time [5,13] allocated to clinical visits and tools to gather a comprehensive understanding of their patients’ needs, values, preferences, goals, and concerns. System-level barriers lead to missed opportunities to individualize care and act upon PCD that might have a substantial impact on patient outcomes and the experience of care [14].

Previous research has demonstrated that patients reveal more sensitive information via health information technology than during patient visits [15]. Studies show that unvoiced concerns and goals for care disproportionately relate to the patients’ experience of illness [16,17], patients’ expectations of treatment [18], or psychosocial concerns [17,19-21]. These *contextual errors* (ie, disregard of PCD in care planning) [14] are more costly to the health care system than biomedical errors (ie, guideline-discordant care) [11]. Conversely, when providers incorporate PCD into the care context, patients’ engagement in their self-management and adherence to the agreed-upon care plan increases [22]. Furthermore, when the health care team collects and incorporates PCD during a visit, it facilitates rapport building and aligns patient and provider goals [5].

### Strategies to Mitigate Disparities

Research indicates that there are ethnic and racial differences in the adoption of consumer informatics tools [23-26]. In a study of a national sample of US adults, ethnic and racial minorities were less likely to be invited to use a patient portal than ethnic and racial majority populations [27]. Furthermore, individuals who did not use a patient portal were more likely to be unemployed, receive Medicaid insurance, have less than a college-level education, did not have a regular health care provider, were male, and aged 65 years or above [26]. As patient portal usage has been shown to be associated with improved quality measures and is thought to contribute positively to patient safety, digital tools should be assessed for their capability to be adopted by a wide range of the population and to narrow, rather than grow, the gaps in care across groups [28].

Given that disparities exist in the adoption and use of consumer informatics tools [27,29,30], researchers must evaluate ways to reach vulnerable populations when testing new consumer information technologies. Current trends suggest that internet access is no longer the main cause of the digital divide [31]. Instead, some patients lack the knowledge, skills, and confidence in using technology [32]. Providers may be key to reduce differences in consumer technology use by inviting all patients to use the new technology, discussing privacy and security concerns and providing resources tailored to a low health literacy level, on use [26]. Additional strategies to reach the most vulnerable individuals and across racial groups include developers employing patient-centered design strategies such as a simple, clean, and aesthetically appealing interface [33]; incorporating patient education on how to use the technology [34]; and promoting the new technology in various ways [35]. Conceivably, introducing a new consumer informatics technology designed to improve patient activation and communication may not achieve the desired rates of adoption, unless health care team members actively promote and assist in the use of the technology [8,25,35,36].

### Study Objectives

In this randomized controlled trial, we aim to evaluate the influence of PCD, collected using a consumer informatics tool, for previsit planning and routine clinical visit discussions with the health care team. The goal is to compare postvisit patient-provider communication and changes in patient activation among patient users and nonusers of the PCD tool, accounting for differences between non-Hispanic White and Black participants (hereafter White and Black). We will measure these constructs using 2 validated measures, the Communication Assessment Tool (CAT) [37] and the Patient Activation Measure (PAM) [38]. Furthermore, we will evaluate the impact by race by determining whether PCD could help mitigate any baseline differences in patient activation and postvisit patient-provider communication between White and Black patients.

We hypothesize that inviting patients directly to submit this information may help with several factors, including activation (patient ready to manage their health and care) and communication (helps prepare perspective and helps the clinician identify salient points).

The primary aims of this trial are to (1) assess the effects of using PCD on patient-provider communication (primary outcome) and patient activation (secondary outcome) and examine whether the effects are different for Black and White patients, accounting for age, gender, and other patient factors and (2) evaluate whether baseline measures of patient-provider communication and patient activation modify the effectiveness of PCD in improving either outcomes, accounting for age, gender, and other patient factors.

We have 2 outcomes of interest: (1) patient-provider communication measured using the CAT [37] and (2) patient activation measured using the PAM [38].

## Methods

### Study Design

This trial will assess the impact of incorporating PCD on patient-provider communication and patient activation of Black and White participants. The trial is registered at ClinicalTrials.gov (NCT03766841). The health network’s ethics review board approved this trial (registered project PRO00031177). The study protocol adheres to the Standard Protocol Items: Recommendations for Interventional Trials (SPIRIT) 2013 [39] checklist (Multimedia Appendix 1).

Using an experimental study design, we will recruit a prospective cohort of eligible Black and White patients from primary care clinic sites randomized to intervention (invitation to use the PCD tool with facilitated enrollment) or usual care (invitation to use the PCD tool only) and administer questionnaires at baseline and after their primary care visit. The questionnaires assess the perceptions of visit communication and patient activation. The survey results will be adjusted for previsit measures of communication as the CAT [37] is only validated as a postvisit measure of patient-provider communication. Figure 1 presents the randomized controlled trial study design.

**Figure 1 figure1:**
[figure not shown]
Randomized controlled trial study design.

### Sample Size Determination and Randomization

An a priori power analysis was performed to estimate the required sample size using G*Power 3 [40,41] based on the study’s primary outcome, the CAT [37]. These were conducted for the more straightforward two-sample *t* test procedure, as this is known to yield a conservative assessment of power. For a two-sided test at α=.05, a total sample size of 200 results in 80% power for a standardized effect size of 0.4 and 94% power for an effect size of 0.5. Increasing the sample size to 250 raises the power to 88% and 98%, respectively. A sample size of 250 provides 79% power to detect a standardized effect size of 0.35. To account for up to 20% potential dropout over time, we aim to enroll 300 participants (targeting 150 Black and 150 White participants). Once participants provide consent, REDCap (Research Electronic Data Capture) [40] will randomize them into 1 of 2 experimental arms: (1) PCD tool (ie, facilitated enrollment for PCD tool intervention) or (2) usual care (ie, email invitation only for PCD tool). We will use stratified random sampling to ensure equal representation of Black and White participants in each arm. Stratified randomization prevents an imbalance of racial representation between arms.

### Randomization of Study Participants

#### Allocation Process

An allocation table was created using R to develop a block randomization scheme to balance arms and stratification by race. The block randomization scheme was then incorporated into the REDCap [40] system. Randomization is stratified by race in a 1:1 ratio, ensuring that we oversample Black participants based on population demographics. Blinding does not occur for either the participant or the study team. Participants are invited to join a communication study but are not told whether the study will focus on their use of the PCD tool.

#### Study Population

A total of 300 adults (≥18 years) with established primary care providers (ie, at least one visit in the previous 12 months with the same provider) from 2 academic and community-based primary care clinics of the Medical College of Wisconsin in Milwaukee, Wisconsin, United States, will be recruited for the study.

#### Inclusion Criteria

Eligible participants are individuals (1) aged 18 years or above, (2) who self-identify as non-Hispanic White or Black, (3) who speak and understand English, (4) who are willing and able to give informed consent, and (5) who at the time of the study enrollment period have an upcoming visit (1-4 weeks away), (6) whose appointment at one of the academic medical center’s primary care clinics, and (7) whose appointment is with an established provider (at least one previous appointment with the same provider within the last 12 months).

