#### PCD Tool Arm

After completion of the previsit survey, all participants in the intervention group will receive an email with a link to the PCD tool for participants to complete their profile. Participants are given the option to complete their PCD profile independently or with assistance from one of the research staff. Providing the participant with options to complete their PCD profile ensures that the participant has access to the internet and a device. Facilitating the enrollment process may also overcome the current rates of adoption and use of the tool (4.7% in 2018) by being responsive to participants’ varying degrees of computer literacy and technical skills.

For participants who do not have an email address and decline to sign up for one, a paper survey will be used to collect the PCD and share them with the health care team at the time of the appointment. Although completion of a paper form loses some of the elements of the trial (PCD not integrated into the EHR), it decreases the chances of adding bias in the study as Blacks are less likely than Whites to have an email account [32,46].

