#### Usual Care Arm

Participants randomized to the usual care arm will complete their previsit survey, scheduled primary care visit, and postvisit survey. The only information regarding the PCD tool they receive before their visit is the email sent automatically by the EHR system to all patients at the academic medical center to create or update their PCD account 1 week before their appointment. For participants who did not have a previsit survey completed at least five days ahead of the appointment, a study team member will give a call to remind the participant to complete the survey as soon as possible. For participants who indicate a preference to complete the previsit survey over the telephone or in person, the study team member will read the survey items verbatim and complete the survey in REDCap.

For both arms, after the scheduled primary care clinic visit occurs, participants will receive up to 3 email reminders to complete the postvisit survey. A study team member will give a call to remind the participant to complete the postvisit survey if it is not completed after the third email reminder. For participants who indicate a preference to complete the postvisit survey over the telephone or in person, the study team member will read the survey items verbatim and complete the survey in REDCap.

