We will collect the following independent variables in the previsit survey: CG-CAHPS communication composite [47], Patient-Reported Outcomes Measurement Information System (PROMIS) Global Health [49], health literacy [50], technology use or technology acceptance [51], and sociodemographic characteristics. We will measure previsit patient-provider communication using the communication composite of the CG-CAHPS survey [48]. The CG-CAHPS communication composite has high internal consistency (Cronbach α=.89) [47], which was determined using a nationally representative sample of over 21,000 patients from 450 US practice sites. We will assess participants’ perceptions of their global health using the PROMIS 10-item Global Health Short Form, which includes scores on global physical health and global mental health. The PROMIS 10-item Global Health Short Form scales had internal consistency reliability coefficients of 0.81 for global physical health and 0.86 for global mental health in a large national survey [49]. Technology use or technology acceptance will be collected using the Health Information National Trends Survey 5, Cycle 1 [51]. Participants will report health literacy using a validated one-item tool [50]. Sociodemographic characteristics and other hypothesized predictors of the outcome measures include income, age, sex, gender identity, health insurance status, educational attainment, number and type of chronic conditions, and length of relationship with primary care provider (in months or years).

We will monitor the use of the PCD tool in 3 ways. First, we will assess whether those in the PCD tool arm completed their profile before their appointment. Second, for participants in the usual care arm, we will determine if they created a profile after they entered the study, as all patients in the academic medical center have access to the PCD tool. Third, we will assess whether any of the care team members reviewed the participant’s PCD tool profile within one day before the appointment and on the day of the appointment. Figure 3 displays the Randomized Controlled Trial Standard Protocol Items: Recommendations for Interventional Trials (SPIRIT) [39] including an overview of study time points, intervention, and assessments of the randomized controlled trial.

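### Existing PCD tool users are not screened out, and tool use is counted differently in the two arms, so the treatment-on-the-treated estimate is biased toward zero

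*Protocol article*

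**What the plan says.** **Eligibility.** The Protocol article lists seven inclusion criteria. The last requires a patient "whose appointment is with an established provider (at least one previous appointment with the same provider within the last 12 months". None concerns an existing profile, and the article states no exclusion criteria. The Recruitment section says that everyone who meets the inclusion criteria will be selected from weekly EHR reports.

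**The tool was live before and outside the trial.** The PCD Tool Arm section refers to "current rates of adoption and use of the tool (4.7% in 2018". The Usual Care Arm section describes an "email sent automatically by the EHR system to all patients at the academic medical center to create or update their PCD account", wording that covers existing accounts as well as new ones. Data Collection explains its usual-care check by access: "as all patients in the academic medical center have access to the PCD tool".

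**How use is measured (Data Collection).** There are three checks:
- PCD arm: whether the profile was completed by the time of the appointment. No earliest creation date is set.
- Usual care arm: whether "we will determine if they created a profile after they entered the study".
- Whether the care team opened the profile, from one day before the visit through the visit day.

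**How use is analyzed (Analysis).** The primary analysis is ITT. A TOT effect is then estimated by two-stage least squares, with tool use during follow-up as the first-stage variable. The section anticipates crossover after randomization: intervention patients who complete no profile and usual-care patients who create one. It does not mention profiles that existed before randomization.

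**The concern.** The eligibility rules let in patients who already hold a profile, and the use checks treat such patients differently by arm. Take two identical patients, each with a profile completed a year before enrollment. The one assigned to the PCD arm has a profile completed before the appointment and counts as a user. The one assigned to usual care did not create a profile after study entry, so the check for that arm does not find it.

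Randomization balances prior users between the arms in expectation. Under a common definition of use they would largely cancel out of the first-stage difference. Under the stated checks they do not cancel: they add to apparent uptake in one arm only. The TOT estimate is the ITT effect divided by the uptake difference, so an inflated denominator understates the effect of using the tool. That effect is the users-versus-nonusers question posed in Study Objectives. A lesser consequence is some dilution of the ITT contrast.

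**Working it through.** **Inputs.** Prior-use share p = 0.047 (PCD Tool Arm, 2018 system-wide rate). Enrollment 300; two-sided α = .05; N = 250 with d = 0.40 and 0.35 (Sample Size Determination and Randomization). The article gives no expected uptake by arm, so the true uptake difference D is an assumption, taken as 30 to 70 points.

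**1. The plan's own power figures.** Two-sample t test, noncentral t, 1:1 allocation:

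| N | d | Stated | Recomputed |
|---|---|---|---|
| 200 | 0.40 | 80% | 80.4% |
| 200 | 0.50 | 94% | 94.0% |
| 250 | 0.40 | 88% | 88.3% |
| 250 | 0.50 | 98% | 97.6% |
| 250 | 0.35 | 79% | 78.7% |

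They reproduce.

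**2. Expected number of prior users.** 300 × 0.047 = 14.1, or about 7 per arm, if enrollees resemble the 2018 population.

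**3. First-stage bias.** Let u1 and u0 be uptake among patients without a prior profile in the PCD and usual care arms.
- Common definition (profile available by the visit): PCD arm p + (1 − p)u1; usual care p + (1 − p)u0. Difference D = (1 − p)(u1 − u0).
- Checks as written: PCD arm p + (1 − p)u1; usual care (1 − p)u0. Difference D + p.

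If use instead means activity during follow-up, let v1 and v0 be the shares of prior users who update in each arm. The PCD arm is overcounted by p(1 − v1) and usual care is undercounted by p·v0. The total error is p(1 − v1 + v0), which is at most p when v1 ≥ v0. So p is an upper limit under either reading.

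**4. Effect on the TOT estimate.** With the ITT effect in the numerator unchanged, estimated TOT ÷ correct TOT = D/(D + p):
- D = 0.70: 0.70/0.747 = 0.937, about 6% too small.
- D = 0.30: 0.30/0.347 = 0.865, about 14% too small.

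**5. ITT dilution, worst case.** Assume facilitation gives prior users no benefit at all, so effective d = d(1 − p):
- d = 0.40: 0.40 × 0.953 = 0.381; power at N = 250 falls from 88.3% to 85.1%.
- d = 0.35: 0.35 × 0.953 = 0.334; power falls from 78.7% to 74.8%.
- If prior users keep half the effect: 0.40 × (1 − 0.0235) = 0.391; power 86.8%.
- If the prior-use share were 10% (assumption): d = 0.36; power 80.9%.

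**The case against.** **The article condenses a fuller protocol, and a filter on existing profiles may exist there.** The usual-care check could even be read as presupposing that nobody has a profile at entry. This is possible, but the article says everyone meeting the listed criteria is selected, and none of those criteria concerns a profile. The asymmetric checks are stated text, not an omission.

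**Admitting existing users is defensible.** The article calls the trial pragmatic, and the randomized contrast is facilitated enrollment against invitation only. This stands. Excluding existing users would change the population studied; it would not correct an error.

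**The first stage is defined by use during follow-up, and the care-team check is not limited by arm or creation date.** This stands in part. A usual-care patient who updates an old profile ought to count under the Analysis wording. But Data Collection specifies no measure of patient use that would capture that update, and the care-team check records clinician viewing, not patient use.

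**Two stronger readings a reader might infer are not supported.** One is that prior users contribute almost no contrast, so the ITT result is seriously weakened. The facilitation section describes staff reviewing all story domains, including the visit agenda, and recontacting patients about completing or updating the profile, so an existing user in the PCD arm can still receive something different. Zero contrast is a worst case, and even that costs about 3 power points at d = 0.40. The other is that the baseline CG-CAHPS and PAM scores are contaminated. Prior users' scores may reflect earlier tool use, but a covariate measured before randomization remains valid for adjustment and as an effect modifier, whatever shaped it.

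**Conclusion.** The point holds for how use is measured. The documents admit prior users, do not identify them, and apply checks that classify identical prior users as users in one arm and nonusers in the other. If those checks feed the first stage, the TOT estimate is understated by up to about 6% to 14%. This rests on three assumptions: that the Data Collection checks supply the use variable, that the 2018 rate of 4.7% applies to the 2019 enrollees, and that the true uptake difference lies between 70 and 30 points. The enrollees' actual prior-use share is not given; a higher share would enlarge the bias.

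The primary ITT comparison is attenuated slightly at most and is not invalidated. Nor do the documents show that criterion 7 selects patients whom the automatic email had already reached, because they give neither the tool's launch date nor the date the emails began.

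**What to change.** Pull profile-creation and update dates for all participants, then:

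1. Define use identically in both arms, for example as a profile available or updated by the index visit, whenever it was created, and use that variable in the first stage.
2. Flag profiles that existed before randomization and report them by arm as a baseline variable.
3. Report a sensitivity analysis of the CAT and PAM arm comparisons that excludes flagged participants from both arms. Because the flag is fixed before randomization, this keeps the randomized comparison intact.

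**Cost.** One data pull. Patients who do not use the portal are linked to the EHR by a statistical matching algorithm, so some dates may need checking. The sensitivity sample is slightly smaller: 250 × 0.953 is about 238, with 86.7% power at d = 0.40. That is only 1.6 points above the worst-case 85.1%, so the main gain is the corrected use variable, not power. Enrollment and analysis are reported as complete, so the sensitivity analysis would be post hoc and should be labeled as such.
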